#### Mindfulness-based stress reduction program

The intervention followed the scheme and instructions of the official MBSR program designed by Kabat-Zinn (2003). Specifically, within the 12 weeks, there was an introduction session, followed by eight intervention sessions and an intensive practice session interspersed between sessions six and seven. The MBSR intervention took place daily, five days a week. Prototypical weeks had one day with a 150-min online session, while participants performed formal and informal practice for 20–40 min the remaining four days. An accredited mindfulness instructor led the program. Participants were provided with a program dossier that included theoretical explanations and instructions for daily practice and audio recorded by the instructor to guide the meditations. A detailed description of the mindfulness intervention following the template for intervention description and replication (TIDieR) guidelines (Hoffmann et al., 2014) is given in the appendices (see Supplementary Material 1).

#### Multicomponent physical exercise program

The PE intervention was designed following Billinger’s recommendations for stroke survivors (Billinger et al., 2014). It consisted of a 12-week program in which five weekly sessions of 45–60 min were done. Three of these sessions were conducted in groups through video-conferencing technology and led by a physiotherapist and a strength and conditioning specialist. The other two sessions were individualized, and participants were asked to walk. A detailed description of the PE intervention following the TIDieR guidelines (Hoffmann et al., 2014) is given in the appendices (see Supplementary Material 2).

#### Computerized cognitive training program

Computerized cognitive training was carried out using the Guttmann Neuropersonal Trainer (Solana et al., 2015), a computerized telerehabilitation platform. The intervention consisted of a multi-domain task program in which different cognitive processes such as executive function, memory, speed, and attention were included. The platform created personalized training based on the scores obtained in the baseline neuropsychological evaluation, age, and educational level. From the cognitive profile established, it was possible to detect the deficits presented by the participant and thus provide specific rehabilitation exercises. The difficulty of the tasks was adjusted according to the participant’s performance and the therapeutic range (i.e., a percentage of correct answers between 65 and 85%). The training was done individually five days a week, and the duration was 45 min per session.

### Intervention adherence

Intervention adherence was counted as the total number of sessions performed (i.e., the summation of face-to-face and autonomous sessions). Instructors recorded attendance at face-to-face classes, while participants filled in a diary whether they had done the independent sessions and any difficulties or inconveniences they may have experienced. Instructors reviewed the diaries weekly and discussed with participants any incidents or questions that may have arised. In addition, in the case of the PE group, participants were provided with a physical activity bracelet (Fitbit Inspire HR^®^) that they wore the whole intervention.

Furthermore, we controlled whether the participant had already taken any of these interventions before entering the study and any other therapy he/she had followed concomitantly with our interventions. For this reason, we created a questionnaire that participants answered at the end of the trial.

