### Interventions

The interventions consisted of five daily sessions per week for 12 weeks and were performed entirely remotely. The mindfulness group received an MBSR program combined with CCT; the PE group received a multicomponent PE program combined with CCT, and the control group only received CCT. The duration of the combined interventions was approximately twice that of the active control group. In the two combined therapy groups, participants did not receive any specific instructions regarding the order in which to perform the interventions.

Mindfulness-based stress reduction and PE interventions included (a) online synchronous sessions guided by expert caregivers and done in groups of 8–12 participants and (b) individual autonomous sessions. In contrast, the control group performed all sessions independently through a computerized telerehabilitation platform. To minimize the confounder effect of benefits from peer interaction and social support in the combined interventions, we invited participants from the same intervention arm to communicate and share experiences through WhatsApp groups.

Before starting the interventions, participants were instructed to use the electronic platforms. Furthermore, they were provided with a manual that collected the main instructions, safety measures to perform the assigned therapies, and a compendium of doubts and frequently asked questions resolved.

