#### Statistical analysis

Statistical analysis will be carried out with IBM statistical package for the social sciences (SPSS) Statistics 27 and R environment. The same statistical pipeline will be run twice, in two sequential phases: (1) intention-to-treat analysis considering data from all randomized participants, including those that complete and drop out of the study (in case of missing values, an adequate method of imputation will be executed whenever appropriate, depending on the proportion of missing data and the missingness mechanisms); (2) per-protocol analysis including only those who have had a treatment adherence equal to or higher than 80%. The significant threshold will be set at a two-tailed *p*-value of 0.05, and an appropriate multiple comparisons correction method will be implemented.

Baseline demographic and clinical characteristics of participants in the different intervention groups will be described with central tendency, dispersion, and position measures and compared between the three groups using parametric or non-parametric tests. To address our primary hypotheses, we will use multiple regression models, which will include: (a) the difference between the follow-up and baseline values in the primary outcome measures as the explained variable; (b) the 3-arms intervention as the explaining variable, and (c) other confounding factors as covariates. We will consider sex, age, years of education, time since stroke, and the baseline score as fixed covariates. Moreover, we will contemplate the need to adjust for further unbalanced factors between groups that appear to correlate strongly with the outcomes. In case of violating the linear regression assumptions, transformations of the variables or methods of robust regression will be adopted. We will examine the secondary outcomes with the same pipeline in the per-protocol sample. Although the sample size was not calculated to allow interaction effects, we will examine potential mediator and moderator effects in this sample.

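### Per-protocol membership rests on self-reported diaries for every computerised training session, so control and MBSR participants can pass the 80% cut with no verified session while PE participants cannot

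*Protocol article*

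**What the plan says.** The section Intervention adherence of the protocol article defines the measure: "Intervention adherence was counted as the total number of sessions performed (i.e., the summation of face-to-face and autonomous sessions". It then names a source for each kind of session. For live sessions, "Instructors recorded attendance at face-to-face classes". For the rest, "participants filled in a diary whether they had done the independent sessions and any difficulties or inconveniences they may have experienced". The stated check on the diary is a weekly conversation: "Instructors reviewed the diaries weekly and discussed with participants any incidents or questions that may have arised". One arm has a further device: "in the case of the PE group, participants were provided with a physical activity bracelet". The section gives no rule for turning bracelet data into sessions and does not mention platform records.

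The section Interventions says that "the control group performed all sessions independently through a computerized telerehabilitation platform". The section on the CCT program describes individual training five days a week, the same in all arms, and adds that "The difficulty of the tasks was adjusted according to the participant’s performance and the therapeutic range", the range being a percentage of correct answers.

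Under Statistical analysis, the second phase is a "per-protocol analysis including only those who have had a treatment adherence equal to or higher than 80" per cent. The primary pipeline is rerun in this set. It is also the stated sample for the secondary outcomes and for the mediator and moderator analyses.

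**The concern.** One threshold is applied to a count whose sources differ by arm. CCT, the only component that all arms share, is delivered by a computer that must process individual performance in order to adapt, yet its sessions are counted from what participants write down. The article itself expects varying degrees of cognitive disability in the sample, so there is reason for care with self-recorded counts.

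If diaries overstate sessions, people who received less than 80% of the dose enter the per-protocol set. What is at stake is the meaning of that set in the per-protocol rerun and in the molecular, brain and behavioural analyses that form the secondary objectives.

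**Working it through.** The article gives no figure for the verified share of the dose, so there is none to reproduce. The sample size of 47 per arm plays no part here.

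**Inputs (protocol article)**
- CCT, all arms: 5 per week × 12 weeks = 60 individual sessions (Computerized cognitive training program).
- PE: 5 × 12 = 60 sessions, of which 3 × 12 = 36 are live classes and 2 × 12 = 24 are walks (Multicomponent physical exercise program).
- MBSR: 5 × 12 = 60 sessions, of which 1 introduction + 8 + 1 intensive = 10 are group sessions (Mindfulness-based stress reduction program).
- Per-protocol cut: 80% (Statistical analysis).

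**Assumptions.** The denominator is all planned sessions pooled: 60 in control and 60 + 60 = 120 in each combined arm. The face-to-face classes are the live online sessions.

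**Sessions by source, as written**

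| | Control | MBSR+CCT | PE+CCT |
|---|---|---|---|
| Planned | 60 | 120 | 120 |
| Needed for 80% | 48 | 96 | 96 |
| Staff-recorded | 0/60 = 0% | 10/120 = 8% | 36/120 = 30% |
| Most that diary entries alone can reach | 60/60 = 100% | 110/120 = 92% | 84/120 = 70% |
| Diary entries needed if every live class is attended | 48/48 = 100% | (96 − 10)/96 = 90% | (96 − 36)/96 = 63% |

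Diary entries alone clear 80% in control and MBSR+CCT, and fall short in PE+CCT.

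**Sensitivity to the assumptions**
- MBSR group sessions: with 9 to 12 in place of 10, the staff-recorded share is 7.5% to 10% and the diary maximum 92.5% to 90%. The conclusion is the same.
- Cut applied to each component separately: CCT is 100% diary in every arm. For the add-on, the diary maximum is 50/60 = 83% in MBSR and 24/60 = 40% in PE. An MBSR participant can still pass on diary entries alone and a PE participant still cannot.

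**What over-reporting could do (assumed, 0 to 20 percentage points).** A control participant who truly did 36 of 60 sessions (60%) needs 48 − 36 = 12 extra entries, or 20 points, to be classed as adherent. One who did 47 needs a single entry.

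**With CCT counted from platform records**
- Verified share: control 60/60 = 100%; MBSR+CCT (60 + 10)/120 = 58%; PE+CCT (60 + 36)/120 = 80%.
- Diary-only maximum: control 0%; MBSR+CCT 50/120 = 42%; PE+CCT 24/120 = 20%.

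No arm could then reach 80% on diary entries alone.

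**The case against.** **The PE arm is less well verified than it looks.** A reader might infer that PE adherence is mostly observed or observable, against pure self-report in control. The figures do not support that. Staff record 36/120 = 30%, and adding the 24 walks worn with a bracelet gives 60/120 = 50%. A majority appears only for the PE component taken alone, or by time with 60-minute PE sessions: 300/(300 + 225) = 57% of weekly minutes. Adherence, however, is counted in sessions over the whole treatment. If platform CCT is called observable, control is 100% observable too. This objection stands.

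**Silence is not exclusion.** A reader might infer that platform and bracelet data are left out of the count. The article does not say so. The bracelet is introduced within the adherence section, and platform records are simply not mentioned; the full protocol may use them. This also stands. But the article does assign a source to independent sessions, and that source is the diary.

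**Unequal sources do not prove unequal misclassification.** A PE participant who truly did 72 of 120 sessions (36 classes and 36 others) needs 96 − 72 = 24 extra entries and has 84 − 36 = 48 missed diary sessions in which to make them. The same over-reporting in percentage points can therefore carry people across the cut in every arm. Any claim about which contrast is biased, or in which direction, fails on this ground. It fails most plainly for MBSR+CCT against control, where diary dependence is 90% against 100%.

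**The remedy does not equalise the arms.** The gap in verified share between control and MBSR+CCT would grow from 8 to 42 points (100 − 58). Between control and PE+CCT it would fall from 30 to 20, and between the two combined arms it would stay at 22. The case for the change is a more accurate count in every arm, not equal verification.

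**Conclusion.** The point holds as a weakness in how per-protocol membership is measured. As written, all CCT sessions in all arms are self-reported, and staff record 0%, 8% and 30% of the planned dose in control, MBSR+CCT and PE+CCT. The same 80% cut can be met on diary entries alone in the first two arms (maximum 100% and 92%) and cannot in the third (70%). The percentages assume pooled planned sessions; the contrast between PE and the other two arms also survives a per-component cut.

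The consequence is possible misclassification in the per-protocol rerun of the primary analysis and in the secondary, mediator and moderator analyses. A reader might go on to infer a bias of known direction against or in favour of a particular arm. The article has no data on diary accuracy and supports no such statement. The intention-to-treat analysis of all randomised participants does not use the adherence count and is unaffected.

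**What to change.** In Intervention adherence, count CCT sessions in all three arms from the platform's usage records where these were retained. Keep the instructor registers for live classes and the diary for MBSR home practice and PE walks. Use bracelet data only as a supporting check, since no rule exists for turning them into sessions. In Statistical analysis, apply the 80% cut to this count, state its denominator, and report the diary-only classification as a sensitivity analysis. If the platform records were not kept, say so, so that readers know what the cut rests on.

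The cost is a data export and a change of wording, with no new patient contact. Data collection ended in December 2021, so the export depends on the records having been kept, which the article does not show. Some participants may leave the per-protocol set and make it smaller. MBSR home practice stays self-reported, so verification remains unequal between arms; the report should acknowledge this.

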### Safety considerations

Our health professional team reviewed each participant’s baseline assessment before randomization to ensure intervention safety (e.g., all candidates must have a physician’s approval to perform PE before enrollment). If any medical incidence was found in baseline assessments (e.g., in the brain scan or blood test), the participant was informed and redirected to the appropriate health service. In these cases, we decided whether the patient should be excluded from participation based on medical recommendations.

Once assigned to a group and before beginning the interventions, participants received an information session and a written manual with the safety measures they should take to avoid injuries or other potential adverse experiences. They were also instructed to spontaneously report any adverse events throughout the study and to fill in a diary with any difficulties or inconveniences they experienced during or after the sessions. Instructors reviewed the diaries weekly and regularly informed the project manager. Any severe event (e.g., fall, fracture) had to be reported immediately to the Principal Investigator and the Institution’s Research Ethics Committee. Adverse effects will be reported in future manuscripts following official guidelines.

### Tailoring participants’ individual needs

Given the breadth of the eligibility criteria, it was anticipated that the sample would have a wide range of ages and varying degrees of physical and cognitive disability. For this reason, before starting any evaluation or intervention, we determined the individual needs of each participant. Based on these, we decided on the necessary accommodations, which could involve a more comprehensive initial training in digital technologies or specific physical, linguistic, and cognitive adaptations. For example, in the case of people with mild to moderate aphasia who had impaired reading ability, self-administered questionnaires were applied orally by an expert interviewer. Supplementary Materials 1, 2 provide complete information about the adaptations made during interventions.

## Data management and results

### Confidentiality and access to data

Each participant was identified with a dissociated alphanumeric code assigned according to the order of inclusion (i.e., when the patient signed the informed consent). The principal investigator and the project manager kept a confidential record of the participant’s personal information and their assigned identification codes. All trial data was incorporated anonymously in a database stored in an institutional server that requires a password to be accessed (i.e., a strong password consisting of aleatory numbers, upper and lowercase letters, and symbols). Once the database is completed, a double-check process and an assessment of its quality will be carried out. After results publication, data will be shared in anonymized form upon reasonable request.

### Baseline variables

Demographic data (i.e., age, gender, marital status, education, race/ethnicity, employment status, family income) was obtained at baseline through an online questionnaire answered by the participants. Further questionnaires were administered to ascertain cognitive reserve (Rami et al., 2011), personality (Costa and McCrae, 2008), adverse childhood events (World Health Organization, 2020), and expectations about treatment improvements. The Vocabulary and Matrix Reasoning subtests of the Wechsler Adult Intelligence Scale-III (Wechsler, 2001) were administered during the baseline neuropsychological assessment to estimate premorbid intelligence.

The physician in charge of the medical evaluations recorded the existence of current or previous diagnoses apart from stroke, stroke characteristics (e.g., type, evolution time), the specific medication taken by each participant, and smoking and alcohol consumption habits. Moreover, the physician assessed the different neurological symptoms present through the National Institute of Health Stroke Scale (Montaner and Alvarez-Sabín, 2006) and the functionality with the Barthel index (González et al., 2018) and the modified Rankin Scale (Fernández Sanz et al., 2021).

### Outcome variables

#### Primary outcomes

##### Cognitive functioning

All participants completed a comprehensive neuropsychological assessment. We will create z-score composites for each cognitive domain from normalized raw data, as well as a global cognitive function score based on the sum of all domains (see Table 3). Domains will be created following a theoretical-driven approach based on the literature (Lezak et al., 2012). We will consider the changes in cognitive domains and global cognition as primary outcome measures.

**TABLE 3 T3:** Neuropsychological assessment and proposed cognitive composites.

Composite		Test-subtest
Attention–Speed	Attention	Wechsler Adult Intelligence Scale III–Digits Forward (Wechsler, 2001)
		Trail Making Test–A (Tombaugh, 2004)
	Speed	Wechsler Adult Intelligence Scale III–Digit symbol coding (Wechsler, 2001)
Executive functions	Inhibition	Stroop Color and Word Test–Interference (Golden, 2001)
	Flexibility	Trail Making Test–B (Tombaugh, 2004)
	Fluency	PMR phonological verbal fluency (Peña-Casanova et al., 2009)
		Semantic verbal fluency of animals (Peña-Casanova et al., 2009)
	Working memory	Wechsler Adult Intelligence Scale III–Digits Backward (Wechsler, 2001)
Language		Boston Naming Test (15-items) (Goodglass et al., 2001)
Memory	Verbal memory	Rey Auditory Verbal Learning Test–Total learning (Schmidt, 1996)
		Rey Auditory Verbal Learning Test–Delayed recall (Schmidt, 1996)
	Visual memory	Rey-Osterrieth Complex Figure–Memory accuracy (Rey, 2009)
Visuospatial functions		Rey-Osterrieth Complex Figure–Copy accuracy (Rey, 2009)

##### Emotional wellbeing

Depression, anxiety, and stress levels were measured through the Beck Depression Inventory (Sanz et al., 2003) and the Depression Anxiety Stress Scale (Bados et al., 2005). Detailed information on these questionnaires is provided in Table 4. We will consider the changes in these questionnaires’ total scores as primary outcome measures.

**TABLE 4 T4:** Questionnaires.

Name	No. of items	Domain or domains assessed
Beck Depression Inventory-II (Sanz et al., 2003)	21	Depressive symptoms
Childhood Adverse Experience International Questionnaire (World Health Organization, 2020) (baseline only)	36	Adverse childhood experiences
Clinical Outcome in Routine Evaluation-Outcome Measure (Feixas et al., 2012)	34	Psychological distress with four domains: subjective wellbeing, problems/symptoms, general functioning, and risk
Cognitive Reserve Questionnaire (Rami et al., 2011) (baseline only)	8	Cognitive reserve estimation based on proxies
Concomitant Therapies Questionnaire (post-intervention only)	15	Registry of other therapies that the participants follow concomitantly with the study interventions
Demographics and Health History (baseline only)	50	Demographics, medical story, consumption of alcohol and tobacco, COVID-19 data (infection and vaccination), female reproductive health (only in women), data important for microbiome analysis
Depression Anxiety Stress Scale (Bados et al., 2005)	21	Depressive, anxiety, and stress symptoms
Dysexecutive Questionnaire (Pedrero Pérez et al., 2009)	20	Dysexecutive symptoms
Expectancy Questionnaire (baseline only)	10	Expectations about treatment improvements in cognition, emotional wellbeing, physical fitness, and quality of life due to study interventions
Fatigue Assessment Scale (Cano-Climent et al., 2017)	10	Physical and psychological aspects of fatigue
Five Facet Mindfulness Questionnaire (Aguado et al., 2015)	39	Five factors of mindfulness: observing, describing, acting with awareness, non-judging of inner experience, and non-reactivity to inner experience
Food Frequency Questionnaire (Vioque and Quiles, 2003)	93	Frequency consumption of specific foods
Mediterranean Diet Adherence screener (Martínez-González et al., 2012)	14	Adherence to the Mediterranean diet
Memory Failures in Everyday Questionnaire (Montejo Carrasco et al., 2012)	28	Memory failures in daily life
Mindfulness Attention Awareness Scale (Soler et al., 2012)	15	Mindfulness (especially the “acting with awareness” component)
NEO Five-Factor Inventory (Costa and McCrae, 2008) (baseline only)	60	Five factors of personality: openness to experience, conscientiousness, extraversion, agreeableness, and neuroticism
Perceived Changes Questionnaire (post-intervention only)	10	Participants’ subjective experienced changes in cognition, emotional wellbeing, physical fitness, and quality of life due to interventions
Pittsburgh Sleep Quality Index (Royuela Rico and Macías Fernández, 1997)	19	Seven components of sleep quality: subjective sleep quality, sleep latency, sleep duration, habitual sleep efficiency, sleep disturbances, use of sleeping medication, and daytime dysfunction
Profile of Mood States-fatigue subscale (Andrade et al., 2013)	7	Mood states related to physical and psychological aspects of fatigue
Psychological Wellbeing Scales (Díaz et al., 2006)	29	Six factors of psychological wellbeing: self-acceptance, positive relations, autonomy, environmental mastery, purpose in life, and personal growth
Rating Scale for Attentional Behavior (Ponsford and Kinsella, 1991)	14	Attentional behavior in daily life
Reduced Minnesota Leisure-Time Physical Activity Questionnaire (Ruiz Comellas et al., 2012)	6	Physical activity
Stroke-specific Quality of Life Scale (Fernández-Concepción et al., 2008)	38	Eight dimensions of stroke-related quality of life: physical state, communication, cognition, emotions, feelings, basic activities of daily living, ordinary activities of daily living, and family functions
World Health Organization Quality of Life (Abbreviated form) (Lucas-Carrasco, 2012)	26	Four dimensions of quality of life: physical health, psychological health, social relationships, environment

